## Background

Chronic obstructive pulmonary disease (COPD) has become a major public health problem worldwide because of its high and increasing prevalence, morbidity and mortality [1,2]. A recent report estimated that the global prevalence of COPD (stage II or over) is about 10% (12% in men and 9% in women) [3]. In China, COPD affects 8% of the population aged 40 and above [4], and is one of the top diseases in the World Health Organization’s ranking of burden of diseases [5]. It is therefore necessary to develop a reliable intervention strategy for the prevention and management of COPD to reduce the burden of this disease.

Current interventions for COPD (such as smoking cessation, rehabilitation, nutrition support, drug treatments and psychosocial aids) are mainly on a case-by-case basis among patients who have already developed moderately or severely symptomatic COPD, while little attention has been paid to earlier stages of the disease or before it has developed. Although there has been some progress with case-based or hospital-based interventions [such as improvements in exercise capacity, forced expiratory volume in 1 s (FEV_1_) and health-related quality of life, fewer hospital admissions and acute exacerbations, and lower all-cause mortality] [6-9], such efforts for the prevention of COPD are limited among the general population in China. Few patients are diagnosed until they develop severe symptoms and signs, and pulmonary function tests are not routinely performed.

Traditional Chinese medicine (TCM) is very popularly used for COPD in Asia, and reportedly TCM may have some advantages in relieving symptoms, reducing the incidence of COPD exacerbations and improving the quality of life for COPD patients [10,11].

We report in this article on a multi-center, randomized, double-blinded, placebo-controlled trial of traditional Chinese medicine treatment with syndrome differentiation to test the hypothesis that patients with COPD will benefit from the therapy with TCM.

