### Sample size

The sample size calculation is based on the annual decline of mean forced expiratory volume in 1 s (FEV_1_) in COPD subjects. The previous study showed that the mean rate of change in FEV_1_ was a decline of 51 ml per year in patients with TCM treatment and 131 ml per year in patients with usual care with mild/moderate COPD. According to the sample size of the estimation formula $n=2{\left[\frac{(u_{a}+u_{\varphi })\sigma }{\delta }\right]}^{2}$, n1 = n2 = 2(1.64 + 1.28)^2^ × 0.28^2^/0.08^2^ = 209. It is estimated that a sample size of 209 subjects per group will be required, considering 20% drop out and exit. This results in 504 in total. Intention-to-treat analysis will be applied to minimize bias due to drop-outs.

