#### Adverse event reporting

pirometry at each site will be conducted using SpiroUSB™ (CareFusion) and Spida5® software. Routine calibration and standard operating procedures will be uniformly undertaken at each site. Participants will be advised not to use respiratory medications for several hours prior to their spirometry testing. Two sets of measurements will be taken at each visit, pre-bronchodilator and post-bronchodilator (post 400 μg of inhaled salbutamol).

Any adverse events will be listed in the trial record and followed up to completion by the trial coordinators and respiratory physicians. Adverse event details will be scored using a six-point scale: 0 = none, 1 = minimal, 2 = mild, 3 = moderate, 4 = severe and 5 = extremely severe. Participants will be able to report adverse events anytime throughout the trial and will receive advice accordingly. Serious adverse events will be reported to the reviewing Human Research Ethics Committee (HREC) and site HRECs within the timeframe specified by the lead HREC.

Throughout the study period, trial coordinators will contact the participant’s usual treating doctor to record relevant data on presentations and exacerbations.

To assist with outcome documentation and medication compliance, participants will be given a participant diary for the duration of the trial. They will be asked to record trial medication and relief medication usage as well as any new medications they commence during the trial.

Participants may withdraw from the study for any reason at any time without repercussions. They will only be withdrawn by investigators if it is deemed medically unsafe for them to continue. Dropouts will not be replaced.

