### Statistical analysis

Descriptive statistical analysis will be performed for all the study variables. We will calculate the mean, median and standard deviations for quantitative variables, and the absolute and relative frequency for qualitative variables.

We use SPSS 19.0 (license no.: 6f1d84c801f1e6010dc, SPSS Inc., Chicago, IL, USA) to statistically analyze the data. An intention-to-treat analysis will be applied using the Last Observation Carried Forward (LOCF) method. Analysis of covariance with baseline as covariate will be used to assess differences in treatment outcomes between the two groups at each of these time points. To correct for inflated risk of type 1 error, multiple comparison procedures suggested by Ludbrook et al. will be used [16]. The use of relief medication during the trial will be investigated for its effect on the outcome measures by using it as a covariate in the statistical analysis. A Data Safety Monitoring Board has been established to assess the progress of the trial, particularly safety endpoints.

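### Relief-medication use during the trial, which treatment may change, is planned as a covariate, and the plan does not exclude reading a treatment effect from that model

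*Protocol article*

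**What the plan says.** The Statistical analysis section of the protocol article gives the main between-group method as follows: "Analysis of covariance with baseline as covariate will be used to assess differences in treatment outcomes between the two groups". Baseline is the only covariate named there. The analysis principle is also stated: "An intention-to-treat analysis will be applied using the Last Observation Carried Forward (LOCF) method".

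After a sentence on multiplicity, the same paragraph adds: "The use of relief medication during the trial will be investigated for its effect on the outcome measures by using it as a covariate". It refers to the outcome measures in general and exempts none, so both primary outcomes (FEV1 and exacerbation frequency) are covered.

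The timing of this variable is clear from the Adverse event reporting section. Participants keep a diary for the whole trial: "They will be asked to record trial medication and relief medication usage as well as any new medications they commence during the trial". The covariate is therefore measured after randomisation.

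**The concern.** The Background section gives the reason for expecting benefit: "TCM may have some advantages in relieving symptoms, reducing the incidence of COPD exacerbations and improving the quality of life". If that is right, patients on active granules may need less relief medication, and relief use becomes partly a consequence of treatment. Holding it fixed compares active and placebo patients who happened to need the same amount of relief. Randomisation did not create those groups. Two things can then go wrong:

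- Any part of the treatment effect that runs through relief use is taken out of the contrast.
- Where underlying severity drives both relief use and the outcome, conditioning on relief use introduces a difference in severity between the arms being compared.

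For exacerbations the link is closer still, since rising relief use is plausibly part of the event being counted.

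At stake is which number is reported as the treatment effect. The paragraph promises an intention-to-treat analysis, and a contrast conditioned on a consequence of assignment does not estimate that effect. With two models and no stated priority, the choice between them could also be made after the results are seen.

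**Working it through.** **The plan's own figure.** The Sample size section takes "a decline of 51 ml per year in patients with TCM treatment and 131 ml per year in patients with usual care", a difference of 131 − 51 = 80 ml per year, with SD 0.28 L. It computes "2(1.64 + 1.28)^2^ × 0.28^2^/0.08^2^ = 209". Check: 2 × 2.92² × 0.0784/0.0064 = 2 × 8.5264 × 12.25 = 208.9, rounded up to 209 per group. The figure is reproduced and is not in dispute. It supplies the 80 ml and 280 ml used below.

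**Inputs the documents do not give.** The article states no relief-use frequency, no expected difference between arms and no correlation with FEV1. The following are assumptions: treatment lowers relief use by a = 0.1 to 0.3 SD, and the within-arm correlation r between relief use and FEV1 change is 0.2 to 0.4 in size.

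**Formula.** Put relief use M on a scale with within-arm SD 1, so the treatment shift in M is −a. In a linear model the adjusted contrast equals the total effect minus (within-arm slope of outcome on M) × (shift in M). The slope is 280 × r, so

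adjusted contrast = 80 − (280 × r) × (−a) = 80 + 280 × r × a.

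**Case 1: severity raises relief use and lowers FEV1 (r negative).**
- a = 0.1, r = −0.2: 80 − 280 × 0.2 × 0.1 = 80 − 5.6 = 74.4 ml
- a = 0.3, r = −0.4: 80 − 280 × 0.4 × 0.3 = 80 − 33.6 = 46.4 ml

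**Case 2: a benefit of relief medication on the outcome dominates (r positive).** The same sizes give 80 + 5.6 = 85.6 ml and 80 + 33.6 = 113.6 ml. The sign of the bias is thus not settled in advance.

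**Simulation check of case 1.** Relief use was −a × treatment + 0.6 × severity + 0.8 × noise (within-arm SD 1). FEV1 change fell by g litres per SD of severity, with total SD 0.28 L. Relief use had no effect of its own on FEV1. By algebra the bias is −0.6 × g × a. Contrasts in ml:

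| a | g (L) | Bias by algebra | True 80: unadjusted | True 80: adjusted | True 0: unadjusted | True 0: adjusted |
|---|---|---|---|---|---|---|
| 0.2 | 0.10 | −12 | 80.5 | 68.6 | 0.1 | −12.0 |
| 0.2 | 0.15 | −18 | 79.8 | 61.8 | 0.5 | −17.5 |
| 0.4 | 0.10 | −24 | 79.5 | 55.2 | −0.6 | −24.7 |
| 0.4 | 0.15 | −36 | 80.3 | 44.5 | 0.3 | −35.7 |

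The unadjusted contrast stays at the true value throughout. The adjusted one is off even when there is no true effect on FEV1. When a = 0 (treatment does not change relief use) or g = 0 (no shared severity, and here no effect of relief use itself), the two contrasts agree.

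**The case against.** The strongest reply is that the plan already has a sound effect model. The sentence that fixes the between-group comparison names baseline alone. The relief-medication sentence comes separately and states a different aim, namely to investigate what relief use does to the outcomes. Read that way, it is a supplementary analysis, and labelling supplementary analyses is commonly left to a statistical analysis plan, which is not shown here.

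Much of this stands. A reader might infer that the primary treatment effect will be taken from a relief-adjusted model. The article does not say that, and its main sentence points the other way. What does not fall away is that adjustment for a post-randomisation variable is a stated method and not an omitted detail. It is described as part of the analysis of the outcome measures, with nothing to bar a treatment contrast from being read off it. An analysis plan that followed the article would carry this forward.

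A second reply concerns direction. A reader might infer that the adjustment is bound to shrink the treatment effect. It is not. The fall from 80 ml to between 74 and 46 ml needs a shared severity factor, and in that model relief use does nothing to FEV1 itself. The result therefore illustrates confounding and does not show an effect removed along a causal path. A beneficial effect of relief medication would push the other way. This objection stands in full.

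A third reply is that the Adverse event reporting section advises participants to avoid respiratory medication for several hours before spirometry, and FEV1 is also measured after salbutamol. That weakens a direct short-term path from relief use to measured FEV1. It does not remove confounding by severity, and it does not bear on exacerbations, dyspnoea or quality of life.

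**Conclusion.** The point holds in a limited form. The article plans to adjust outcome analyses for a variable measured after randomisation that treatment may change, and it does not confine this to a model from which no treatment effect is read. A treatment contrast from such a model would not be the intention-to-treat effect promised in the same paragraph, and it could be biased either way.

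Confidence is high on the principle and low on the size. The range of 74 to 46 ml against a true 80 ml is an illustration built on assumed shifts and correlations in a shared-severity model. If treatment leaves relief use unchanged, the adjustment does no such harm, but then it is not needed to remove bias either. The documents do not establish that the primary result will be affected, because the main model as written adjusts for baseline only. The change is still worth making, since the possible bias is material and the cost is trivial.

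**What to change.** Amend the Statistical analysis section in three respects:

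- State that the treatment effect on every outcome is estimated from the model with baseline covariates only, without relief-medication use during the trial.
- Compare diary-recorded relief use between arms as an outcome in its own right, for example as uses per week.
- If a relief-adjusted model is kept, label it exploratory and state that its treatment coefficient will not be interpreted as the treatment effect.

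The cost is a few sentences of wording. The diary already collects the data, and neither the sample size nor the conduct of the trial changes. According to the Trial status section, recruitment stood at 150 patients and was not complete at manuscript submission. The wording should be settled before unblinding.

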## Discussion

Chronic obstructive pulmonary disease (COPD) remains a major public health problem. The aim of COPD treatment should be to decrease symptoms and exacerbations, reduce the risk of hospital admission, increase lung function and improve QOL. Recently, the approach to therapy has focused on symptomatic relief.

Traditional Chinese medicine (TCM), as a system of medicine, has been a form of health care in China and its neighboring countries for several thousand years. Some TCM therapy, such as Tanreqing injections, has been reported to be of some benefit to COPD patients, and could improve the Chinese medical signs and symptoms in patients with AECOPD, reducing airway inflammation and airway mucus hypersecretion [17,18]. Others improve lung function and relieve airway inflammation in patients with stable COPD [19].

Currently, there are no TCM treatments involving syndrome differentiation therapy for COPD patients; therefore, we designed this study. The study will be a large-sample, multicenter, long-term chronic obstructive pulmonary disease study. The data gathered will shed new light on traditional Chinese medicine, especially for COPD treatment.

## Trial status

At the time of manuscript submission, we had recruited 150 patients but not completed the patient recruitment.

## Abbreviations

COPD, Chronic obstructive pulmonary disease; CAT, COPD assessment test; FEV1, Forced expiratory volume in 1 s; FVC, Forced vital capacity; GOLD, Global initiative for chronic obstructive lung disease; LOCF, Last observation carried forward; QOL, Quality of life; RCT, Randomized controlled trial.
